## Abstract

**Background:**

In developing countries like Malawi, further investigation is rare after patients with chronic cough test negative for tuberculosis. Chronic airways disease has presentations that overlap with tuberculosis. However, chronic airways disease is often unrecognised due to a lack of diagnostic services. Within developing countries, referral systems at primary health care level are weak and patients turn to unskilled informal health providers to seek health care. Delayed diagnosis and treatment of these diseases facilitates increased severity and tuberculosis transmission.

The World Health Organisation developed the Practical Approach to Lung Health strategy which has been shown to improve the management of both tuberculosis and chronic airways disease. The guidelines address the need for integrated guidelines for tuberculosis and chronic airways disease. Engaging with informal health providers has been shown to be effective in improving health services uptake. However, it is not known whether engaging community informal health providers would have a positive impact in the implementation of the Practical Approach to Lung Health strategy. We will use a cluster randomised controlled trial to determine the effect of using the two interventions to improve case detection and treatment of patients with tuberculosis and chronic airways disease.

**Methods:**

A three-arm cluster randomised trial design will be used. A primary health centre catchment population will form a cluster, which will be randomly allocated to one of the arms. The first arm personnel will receive the Practical Approach to Lung Health strategy intervention. In addition to this strategy, the second arm personnel will receive training of informal health providers. The third arm is the control. The effect of interventions will be evaluated by community surveys. Data regarding the diagnosis and management of chronic cough will be gathered from primary health centres.

**Discussion:**

This trial seeks to determine the effect of Informal Health Provider and Practical Approach to Lung Health interventions on the detection and management of chronic airways disease and tuberculosis at primary care level in Malawi.

**Trial registration:**

The unique identification number for the registry is PACTR201411000910192 – 21 November 2014

**Electronic supplementary material:**

The online version of this article (doi:10.1186/s13063-015-1068-4) contains supplementary material, which is available to authorized users.

## Background

Among non-communicable diseases (NCDs), respiratory diseases represent a major burden of disease, in particular chronic airways disease (CAD). CAD includes asthma, chronic obstructive pulmonary disease (COPD) and bronchiectasis. Risk factors for these conditions include tobacco-smoking, indoor air pollution from biomass fuels and lower respiratory tract infections.

Chronic or persistent coughing is a frequent clinical presenting feature of both CAD and tuberculosis (TB). Chronic cough is a distressing symptom and a common reason for people to seek health services [1, 2]. Findings from studies conducted in Malawi show that patients presenting with cough exert a huge burden on out-patient department (OPD) services [3], and yet there are many challenges to providing effective care for patients with respiratory symptoms in the OPD [4].

### Chronic airways diseases

COPD is characterised by airflow limitation that is not fully reversible but nonetheless treatable. The World Health Organisation (WHO) estimates that 65 million people have moderate to severe COPD with 5 % of all (3 million) global deaths being attributed to COPD [5]. About 90 % of these COPD deaths occur in low-income and middle-income countries. At the other end of the spectrum, asthma, a chronic inflammatory disorder of the airways, is characterised by episodes of reversible breathing problems (that may be life-threatening) due to airway narrowing and obstruction. These episodes are characterised by coughing, wheezing, chest tightness and shortness of breath. The frequency and severity of these episodes can have a marked impact on the livelihoods and the well-being of those affected [6]. Bronchiectasis is a severe, chronic infection of the lung associated with permanent abnormal dilatation of bronchi [7]. As a result mucus clearance is impaired, leading to accumulation of secretions, bacterial overgrowth and recurrent infections.

Regular therapy of CAD with the rational use of inhaled corticosteroids and bronchodilators can reduce the frequency and severity of exacerbations. To date, inhaled corticosteroids and bronchodilators have not been consistently available for use anywhere in Malawi’s health system, and particularly not at primary care level. Because it is difficult to diagnose CAD without appropriate equipment, unnecessary prescriptions of antibiotics are made for treatment. Where available, inhalers are not used effectively because the patients lack adequate education in their proper use. Some patients are treated empirically for TB (sometimes repeatedly) despite negative sputum smears because of a lack of tools and guidelines for further screening for CAD.

### Tuberculosis

TB is the world’s leading infectious cause of death in adults; approximately 1.4 million deaths out of the 8 million annual TB cases occur per year. TB predominantly affects the respiratory system and chronic or persistent coughing is a cardinal symptom. The Stop TB strategy relies heavily on identifying and treating TB cases from among the large group of patients who seek health care because of persistent coughing. However, TB case detection remains a challenge in most countries [8] and especially across sub-Saharan Africa (SSA). Therefore, adult individuals with chronic respiratory symptoms are potential TB cases and pose a relatively high risk of onward transmission of TB. The WHO estimates that Malawi is detecting only 50 % [9] of infectious TB cases, which is below the global target of 70 % [9].

### The relationship between non-communicable chronic respiratory disease and TB

In developing countries with a high prevalence of TB, only between 10 and 20 % of patients presenting in primary care with persistent coughing will actually have TB. The majority of the remaining 80 to 90 % of patients will be suffering from a wide range of non-communicable chronic respiratory diseases including CAD. A proportion of patients who have TB will also have underlying non-communicable chronic respiratory disease. It is now increasingly recognised that chronic respiratory diseases and TB share risk factors including smoking and low socioeconomic status. It is also recognised that a proportion of patients who have not been treated effectively for TB will develop chronic respiratory diseases, such as bronchiectasis and fibrosis, as a result of the tissue destruction and subsequent scarring [10].

### The impact of chronic airways disease and TB on disability and quality of life

Severe CAD and TB exert disabling effects that reduce quality of life and livelihood opportunities for the affected individuals [11]. It is not known, however, what proportion of patients with COPD are so severely affected as to fulfil international criteria for disability, measured by level and type of activity limitation [12]. People with disabilities face particular challenges in accessing social and health services and have higher risks of disease, including TB infection [13]. These challenges, which include stigma and discrimination, may cause patients with disabilities to fail to access health services, remain in a morbid state, and eventually be caught in a damaging cycle of disability, poverty and ill-health.

### The need for integrating approaches to CAD and TB case detection and treatment

Despite the relationship between CAD and TB, health systems in most developing countries have mainly focused on the detection and cure of infectious diseases including TB. There has been less emphasis on the diagnosis and life-long management of CAD. As a result, patients with chronic cough who do not end up with a TB diagnosis are often frustrated because they are not given a diagnosis, education about their condition or treatment. Given the relationship between TB and CAD, integrated management could reduce the proportion of patients with chronic cough without a diagnosis, reduce costs and reduce multiple visits to health facilities for diagnosis.

For this reason, within the Stop TB strategy framework, WHO and the International Union Against Tuberculosis and Lung Disease (IUATLD) developed the Practical Approach to Lung Health (PAL) strategy. PAL is a patient-centred approach to the diagnosis and treatment of common respiratory illnesses in health care settings other than health centres at primary health care level. Specifically, the PAL strategy aims to improve the quality of respiratory disease management by promoting a symptom-based and integrated approach to diagnosis and treatment. The aim is to ensure standardised service delivery by the implementation of standardised clinical and diagnostic guidelines. The PAL strategy focuses on TB, pneumonia, asthma and COPD.

In Syria and Jordan, where the PAL strategy has been adopted, they have seen improvements in referrals, sputum smear examinations, and a reduction in the prescription of antibiotics for CAD, thereby markedly reducing management costs [14, 15]. In Jordan, Abu Rumman et al. found that the PAL approach decreased the number of drugs prescribed per patient by 12.2 % but increased the prescription of inhalers by 155 % [15]. Similarly, in Syria, Me’emary et al. showed a 14.8 % decrease in the number of drugs prescribed per patient and a decrease of 27.4 % in the proportion of patients who received antibiotic prescriptions [14].

Despite evidence for efficacy, the PAL strategy has not been universally adopted in most developing countries, including Malawi. This may be a result of poor acceptance and lack of political will by the national health authorities, or due to concerns regarding the feasibility of strategy implementation at primary health care facilities which are managed by low-level and middle-level health care workers.

The PAL strategy was designed for use in district hospitals. However, there is some evidence that the approach can be implemented at primary health care levels [13]. The studies in Syria and Jordan, as stipulated above, used qualified medical doctors to implement the PAL strategy. However, it is not clear whether it would be feasible to implement the PAL strategy in primary health care facilities staffed by low-level or middle-level health cadres such as clinical officers, medical assistants and nurses. Nonetheless, similarly adapted PAL approaches Practical Approach to Lung Health in South Africa (PALSA) and Practical Approach to Lung Health in Malawi (PALM) have been implemented in South Africa [16, 17] and Malawi [18], respectively, using low level cadres. However, these studies were primarily interested in assessing the impact of outreach training on the recruitment and retention of staff.

In addition to the feasibility challenges of implementing the PAL strategy in developing countries, access to health services in general, and in particular CAD and TB services, remains a challenge. These challenges are due to both, health system and patient barriers [19]. Health system barriers include inadequately qualified health staff with insufficient training and a lack of equipment and treatments.

Optimal utilisation of the available services is further restricted by patient barriers such as poverty [20], stigma, disability [21], low awareness levels for CAD and TB as well as geographical barriers. These barriers encourage patients to seek care from informal health providers such as traditional healers and grocery shop owners [22]. These informal health providers, in general, lack the knowledge and skills needed to provide appropriate health care information, treatment and referrals to health care centres. As a result, poor people accessing care from informal health providers often experience delays in treatment, waste time and resources, and worse still, experience poor health outcomes [23].

In view of these patient barriers, strengthening community-based structures could not only improve a community’s knowledge on CAD and TB but also service utilisation. Engagement of informal health providers in delivery of health interventions to promote service access is well documented. In Kenya, storekeepers have been used to recognise and treat uncomplicated malaria in children and to refer to health services when needed [6, 7]. In South Africa, storekeepers provided successful supervision of TB treatment – directly observed treatment (DOT) [24, 25]. A previous study in Malawi, conducted by the REACH Trust, demonstrated that storekeepers could promote TB case-finding [26] and further work by the REACH Trust demonstrated that informal providers can be engaged in the provision of integrated TB and HIV services at the community level. We found that these interventions led to improvements in HIV-testing by 61 %, anti-retroviral therapy (ART) access rates by 34 % and diagnostic uptake rates for presumptive TB cases by 15 % (manuscript in preparation).

### Aim

The proposed trial aims to determine the effect of Informal Health Provider and Practical Approach to Lung Health interventions on the detection and management of CAD and TB at primary care level in Malawi.

## Methods - trial design

A cluster level randomised controlled open trial with three arms.

### Trial sites

The trial sites will be in the districts of Dowa and Ntchisi, in the central region of Malawi. A total of 27 primary health centres in the districts will be involved in the trial. Each cluster will include a primary health centre together with the surrounding catchment area. To reduce contamination between clusters there will be a 3-km buffer zone between each cluster. The health facilities have been selected based upon their size according to the number of health workers and type of service offered. Those with in-patient services have been excluded. There are 11 such health centres in Ntchisi and 16 in Dowa district. Private not-for-profit health facilities, which run under the Christian Health Association of Malawi (CHAM), have been included.

### Selection criteria

#### Inclusion criteria for health facilities

Health facilities that offer out-patient services onlyRun by low-level and middle-level health care workers

#### Exclusion criteria

Health facilities offering in-patient servicesHealth facilities run by qualified medical doctors

### Sources of recruitment

A community engagement exercise will be carried out to seek community leader and local community support for the trial. Participants selected for participation in the baseline or follow up household surveys will be visited at their homes and invited to participate.

#### Inclusion criteria for individual participants

All consenting individuals aged 15 and above will be eligible to participate.

#### Exclusion criteria

Individuals below the age of 15 years.According to TB control guidelines those below the age of 15 years are less likely to expectorate sputa for TB screening and they fall into a paediatric groupRefusal to participate in the survey will also be an exclusion criterionVisiting members of the household

### Allocation of interventions

Each cluster (health centre with the surrounding catchment area) that has agreed to participate will be randomly allocated to one of the three trial arms using a computer-generated randomisation schedule with stratification by size of cluster. This randomisation will be performed by the trial statistician using dummy codes ‘A’ ‘B’ and ‘C’ to represent intervention and control groups; to ensure the statistician remains blinded, the identity (allocation) of ‘A’ ‘B’ and ‘C’ will be determined by a person independent of the study.

#### The interventions

*Intervention arm 1* – Health centres implementing the PAL intervention. No informal provider intervention.*Intervention arm 2 –* Health centres implementing the PAL intervention. Informal provider intervention.*Control arm –* No intervention at health centre or informal provider level. Routine standard care will be provided.

#### Detail of the health centre-based PAL intervention in arms 1 and 2

The intervention at health centres will involve training medical assistants and nurses on the PAL guide-lines and use of spirometry for the diagnosis and assessment of airflow limitation in patients presenting with chronic cough. The trial will test the feasibility of implementing PAL strategy and integrating TB screening and CAD at the lowest level in the health system in Malawi. Lessons learnt are expected to influence policy and practice countrywide.

Other indicators to measure impact of the trial will include: occurrence and frequency of hospitalisations due to exacerbations, time lapse between symptom development and diagnosis. For TB patients, changes in this diagnostic delay may be a proxy indicator of health outcomes.

Training of health care providers will include:Training of health centre staff on identifying and managing TB and CADs from amongst those with chronic cough.Introducing the use of standardised registers for patients presenting with chronic cough.Introducing the syndromic approach and spirometry for the diagnosis of airway diseases and TB among patients with chronic cough.Introduction and uninterrupted use of inhalers (bronchodilators and corticosteroids) for patients diagnosed with asthma.Introduction and uninterrupted availability and use of inhalers (bronchodilators) for patients diagnosed with COPD.

The aim is that after training the medical assistants and nurses in the intervention health centres will competently carry out the following tasks:Screen and identify COPD, bronchiectasis, TB and asthma cases among patients presenting with chronic cough to primary health care facilities.Use appropriate screening and diagnostic tools and specimens for the diagnosis of COPD, bronchiectasis, TB and asthma.Make appropriate referral of patients to, and receive corresponding feedback from, secondary referral health facilities in the districts.Perform accurate recording and reporting of all cases using tools for the PAL guidelines.Provide key health messages about TB and CAD as part of the routine health talks.

#### Detail of the informal health provider intervention in arm 2

The intervention directed at the community level in intervention arm 2 will aim to build the capacity of informal health providers (IHPs) to recognise, counsel and refer potential TB and CAD patients in their communities.

Mapping of IHPs in the clusters allocated to intervention arm 2 will be done after randomisation. A qualitative study going on in the neighbouring district of Kasungu to explore how the communities understand IHPs by type and role will inform the trial to use the right definitions of informal health providers. During the mapping exercise distribution of IHPs will be determined prior to selection and training them in order to be within the buffer zones.

This intervention will include:Training of informal health providers in the recognition, counselling and referral of patients with chronic/persistent cough to the primary health facility.Training of informal health providers in prevention of COPD and including smoking cessation.Training informal health providers to support patients with airway diseases so that they adhere to both drug and non-drug therapies and compliance to appointments.Training of local health centre staff and health surveillance assistants to give supervisory support to informal health provider activities.Establishment of referral mechanisms between the community and the health system.

Thus, once trained informal care providers will be required to routinely carry out one or more of the following tasks according to their capacity and prevailing circumstances as part of their daily activities:Recognise selected presentations of chronic cough and potential TB cases among eligible persons, including persons with disability, in their communities.Communicate effectively with patients and members of the public to i) encourage and support positive health-seeking behaviour, ii) provide key health messages about COPD, bronchiectasis, TB and asthma among chronic respiratory diseases and iii) provide reliable information on the available services for these diseases at the primary health care facilities in the area.Advise on appropriate screening and diagnostic specimens for TB diagnosis (e.g. sputum).Recommend and provide appropriate information about COPD, bronchiectasis, TB and asthma to encourage positive health care-seeking behaviour and adherence to specific disease risk reduction measures.Refer to, and receive feedback from local public health services at primary health care level, for all identified cases with CADs and suspected TB cases.Competently record and report on all cases referred to primary health care and activities done in the community.

### Outcome assessments

#### Primary outcome measures

Proportion of the population with a chronic cough who have a diagnosis of TB or airway disease(s) recorded in their health passports.

This has been selected as the primary outcome since this is the most clinically relevant outcome effect measurable immediately downstream of the intervention. This intervention is measurable at the community level, thus requiring a community-based survey to collect outcome data.

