#### Baseline survey

Data on CAD is not routinely collected in the study districts, so to inform the final sample size estimation a baseline survey will be conducted, the purpose of which will be to estimate the proportion of individuals over the age of 15 years in each cluster with (a) evidence of chronic cough-/- wheeze, and (b) a diagnosis in their health passport.

For this baseline survey, it will be assumed that for the study population:(i)the mean household size in the study area will be 4.6(ii) the proportion of individuals over the age of 15 years will be 0.52 (52 %)(iii) so the average number of individuals per household over the age of 15 years will be 4.6 × 0.52 = 2.4

As described in detail in table 1, a 3-stage sampling procedure will be used:Stage 1: a random sample of 27 clusters (health centres with surrounding catchment areas) will be selected and 9 of these randomly allocated to each study armStage 2: 30 villages will be randomly selected from each of these 27 clusters based on sampling probabilities proportional to village population again using Google Earth Pro (Google Inc., Mountain View, CA, USA) to identify villages and to estimate their sizes (total 810 villages: 270 per study arm)Stage 3: a simple random sampling procedure will be applied to select 7 households from each selected village (total 5,670 households: 1,890 per study arm)

All eligible participants in each selected household will be interviewed, giving a total sample of 5,670 × 2.4 = 13,608 individuals (4,536 per study arm); 10 % of these individuals (1,360 in total: 453 per study arm) will be expected to show evidence of chronic cough-/-wheeze.

The precision figures quoted below for this baseline survey use the approximate formula for a 95 % confidence interval ‘1.96 × standard error of prevalence estimate’. In the actual analysis, exact binomial confidence intervals will be computed, but these are asymmetric so unsuitable for presenting a simple indication of the precision levels that will be achieved.

Assuming a prevalence of 10 %, a sample of 4,536 individuals will provide an estimate of the true prevalence of chronic wheeze-/-cough in each individual study arm with a precision of ±0.87 %. Ignoring clustering effects, the 13,608 individuals in all 3 study arms combined will provide a precision of ±0.50 %; adding a design effect size adjustment of 2 to allow for clustering effects, the combined sample will have a precision of ±0.71.

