#### Estimation of impact of PAL alone and PAL + IHP interventions versus control

The calculations presented below use an alpha level of 2.5 % rather than the conventional 5 % to allow for 2 primary comparisons (PAL + IHP versus control and PAL alone versus control).

Exactly the same 3-stage sampling procedure will used as for the baseline survey, except that now 14 households will be selected from each village (total 11,340 households: 3,780 per study arm). As before, all eligible participants in each selected household will be interviewed, giving a total sample of 11,340 × 2.4 = 27,216 individuals (9,072 per study arm); 10 % of these individuals (2,721 in total: 907 per study arm) will be expected to show evidence of chronic cough-/wheeze.

The available evidence indicates that approximately 5 % of symptomatic individuals in the control group post-intervention will have a diagnosis in their health passport. The PAL + IHP intervention will be considered clinically important if it increases the proportion of symptomatic individuals with a registered diagnosis from 5 to 20 %.

With 9 clusters per group and 907 symptomatic individuals per study arm (100 per cluster), this study will have 80 % power to detect a clinically important difference between the PAL + IHP and control groups provided the BCV (between-clusters CV (coefficient of variation)) does not exceed 62.9 %, and will have 90 % power if the BCV does not exceed 54 %.

BCV measures the extent to which the proportion of symptomatic individuals with a registered diagnosis varies between the clusters, and expresses this as a percentage of the average proportion of symptomatic individuals with a registered diagnosis across all clusters combined. In most community interventions, BCV is usually less than or equal 25 % [27] so, even at worst, this element of the study will have over 90 % power.

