#### Data collection and management

The baseline survey will be conducted prior to randomisation and prior to intervention implementation. The follow-up survey will be conducted 1 year after intervention implementation. Data will also be gathered from health centres 1 year after the interventions have been implemented.

Measures will be taken to ensure quality and accuracy of information, which will be collected and reported; these will include: firstly, thorough training of health workers – the training content will include proper recording of diagnoses based on knowledge of presenting symptoms and signs of each condition and the differential diagnoses. In addition health care workers will also be taught about spirometry results so that they acquire understanding to help with them in interpreting spirometry results to make accurate diagnosis. Secondly, the trial clinical supervisor will routinely undertake monitoring of practice in the intervention health facilities to ensure that standards are being followed regarding practice, recording and reporting. Patient health passports, PAL registers at facilities and spirometry records will be assessed during the visits.

The data collected from health registers as digital images will be scanned into an electronic database using Teleform software (Cardiff Software, Sunnyvale, CA, USA) or, if this proves to be technically difficult; the scanned images will be double-entered by trained data entry clerks into an Microsoft Access for windows or Epi-Info 6.04 database, a free software developed by the Center for Disease Control of Atlanta in the United States of America.

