## Discussion

The trial will undertake two cross-sectional household surveys: one at the beginning of the trial, prior to randomisation of clusters, and the second after the interventions have been in place for a year. Although the intervention is health centre-based to improve quality of service the primary outcome measure will be assessed in the communities. Trial data, therefore, will have several sources including cross-sectional household surveys, clinic registers, and patient health passports. Monitoring and supervision tools will be developed to support the completeness and accuracy of these data. A subset of patients will be selected to assess quality and accuracy of diagnosis and patient management.

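### The primary outcome counts diagnoses only among people with a chronic cough one year after an intervention that also treats cough, so the denominator may differ by arm

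*Protocol article*

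**What the plan says.** Under Primary outcome measures, the Protocol article defines the outcome as the "Proportion of the population with a chronic cough who have a diagnosis of TB or airway disease(s) recorded in their health passports". On timing, Data collection and management states: "The follow-up survey will be conducted 1 year after intervention implementation". The Discussion confirms that there is no cohort: "The trial will undertake two cross-sectional household surveys: one at the beginning of the trial, prior to randomisation of clusters", with a second survey after a year of intervention. The section on estimating impact uses the same conditional scale for its control value: "approximately 5 % of symptomatic individuals in the control group post-intervention will have a diagnosis in their health passport".

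The intervention in arms 1 and 2 goes beyond diagnosis. It includes "Introduction and uninterrupted use of inhalers (bronchodilators and corticosteroids) for patients diagnosed with asthma" and "Introduction and uninterrupted availability and use of inhalers (bronchodilators) for patients diagnosed with COPD", and staff are trained to manage TB and chronic airways disease. The Background says that inhaled corticosteroids and bronchodilators "have not been consistently available for use anywhere in" Malawi's health system. Arm 2 adds informal providers who recognise chronic cough, refer, support adherence and give public health messages.

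The follow-up sample size takes 10 % of 9,072 people per arm as symptomatic (907) in every arm, the same share as at baseline. The symptom differs between sections: the outcome names chronic cough, while the survey counts are of people who "will be expected to show evidence of chronic cough-/-wheeze".

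**The concern.** A person diagnosed early in the year whose cough has gone by the survey is in neither the numerator nor the denominator. Detection raises the primary outcome, and recovery after detection can lower it. If recovery differs by arm, the comparison mixes the two, and a small PAL effect could mean poor detection or good treatment. In arm 2, raised awareness could also change how many people report a cough; the documents do not show in which direction or by how much.

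The secondary outcomes do not resolve this. The inhaler outcome is again among people with a chronic cough, the register outcome covers attenders with chronic cough at intervention facilities, and the third is limited to people with disabilities. None counts recorded diagnoses in all surveyed adults across all arms.

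**Working it through.** **Inputs from the Protocol article.** 9 clusters per arm; about 100 symptomatic people per cluster; alpha 2.5 % per comparison; 5 % in control, 10 % under PAL alone, 20 % under PAL + IHP; effects reported as rate ratios. **Assumed, because the document gives no figure:** the share r of diagnosed people, and the share u of undiagnosed people, whose cough has resolved by the survey.

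**Step 1: reproduce the plan's figures.** The unmatched cluster formula for proportions is

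c = 1 + (z_α/2 + z_β)² × [p0(1−p0)/m + p1(1−p1)/m + k²(p0² + p1²)] / (p1 − p0)²

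With c = 9, m = 100 and two-sided alpha 0.025 (z = 2.241), solving for k gives 63.0 and 54.1 % for PAL + IHP and 24.2 and 13.8 % for PAL alone (80 and 90 % power). The plan states 62.9, 54, 24.1 and 13.7 %, so its figures reproduce.

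PAL alone at k = 25 %: the bracket is 0.000475 + 0.000900 + 0.0625 × 0.0125 = 0.002156. Then √(8 × 0.05² / 0.002156) = 3.046, and 3.046 − 2.241 = 0.804, so power is 79 %.

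**Step 2: model resolution.** Observed p′ = p(1−r) / [p(1−r) + (1−p)(1−u)]. With u = 0, the cluster size becomes 100(1 − pr).

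Example with u = 0 and r = 20 % in control, 40 % under PAL:
- Control: 0.04 / (0.04 + 0.95) = 4.0 %, m = 99.
- PAL: 0.06 / (0.06 + 0.90) = 6.3 %, m = 96.
- Ratio 0.0625 / 0.0404 = 1.55. The bracket is 0.001348, √(8 × 0.0221² / 0.001348) = 1.702, and 1.702 − 2.241 = −0.539, so power is about 30 % (29.5 %).

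**Step 3: range, u = 0, k = 25 %.**

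| r control / intervention | PAL alone: observed, ratio, power | PAL + IHP: observed, ratio, power |
|---|---|---|
| 0 / 0 % | 5.0 vs 10.0 %, 2.00, 79 % | 5.0 vs 20.0 %, 4.00, >99 % |
| 30 / 30 % | 3.6 vs 7.2 %, 2.03, 69 % | 3.6 vs 14.9 %, 4.19, >99 % |
| 50 / 50 % | 2.6 vs 5.3 %, 2.05, 57 % | 2.6 vs 11.1 %, 4.33, >99 % |
| 20 / 40 % | 4.0 vs 6.3 %, 1.55, 30 % | 4.0 vs 13.0 %, 3.23, >99 % |
| 0 / 25 % | 5.0 vs 7.7 %, 1.54, 34 % | 5.0 vs 15.8 %, 3.16, >99 % |
| 0 / 50 % | 5.0 vs 5.3 %, 1.05, 2 % | 5.0 vs 11.1 %, 2.22, 89 % |

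**Step 4: let undiagnosed coughs resolve too.** With r = u = 30 % in both arms, 5 versus 10 % is unchanged. With u = 40 % and r = 20 % in both arms, the result is 6.6 versus 12.9 %, a wider difference (6.3 points). With u = 20 % in both arms and r = 20 / 40 %, the result is 0.04 / 0.80 = 5.0 % versus 0.06 / 0.78 = 7.7 %, ratio 1.54. The attenuation of the ratio thus comes from the between-arm difference in r and hardly depends on a common u.

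**Step 5: all surveyed adults as denominator.** Suppose 10 % have had a chronic cough since intervention start and nobody else is diagnosed. The proportions are then 0.10 × 5 % = 0.5 % in control, 1.0 % under PAL and 2.0 % under PAL + IHP, whatever happens to the cough. With 9,072 / 9 = 1,008 people per cluster and k = 25 %, PAL-alone power is about 77 %. That is optimistic: cough prevalence also varies between clusters, which raises k, and diagnoses in people without a cough history would dilute the ratio.

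**The case against.** A reader might infer that the effect is certainly biased towards no difference, and that a real doubling would read as null. The documents do not support that. Equal resolution in all arms does not attenuate the planned rate ratio, and equal resolution in diagnosed and undiagnosed people changes nothing. The near-null case (ratio 1.05) needs half of the diagnosed to recover under PAL and none in control, although control clusters keep routine care, which includes TB diagnosis and treatment. The Background describes COPD as not fully reversible and bronchiectasis as involving permanent airway damage, and people diagnosed late in the year have had little time to recover. These points stand, and they make the last row of the table an extreme bound.

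The 5, 10 and 20 % targets are also stated for symptomatic people, so they can be read as already net of resolution. On that reading the stated power holds, and the losses above apply only if the targets mean detection among everyone who had a chronic cough. The sample-size section calls its assumptions preliminary and plans to revisit them after baseline. This limits the power figures, but it does not remove the mixing of detection and recovery in the estimate.

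Finally, no time window for the cough is stated. That it must be present at the survey is inferred mainly from the reference to symptomatic individuals post-intervention. A question covering the whole year would remove much of the problem. However, recall of a resolved cough may be better among diagnosed people and where informal providers publicise cough, so a recall-based denominator carries its own arm-dependent risk.

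**Conclusion.** The concern holds in a limited form. The primary denominator is measured after randomisation, the intervention can change it, and the sample size allows for no such change. The rate ratio is biased towards no difference if diagnosed people recover more often in the intervention arms than in control. The newly supplied inhalers make that plausible, but no figure in the document establishes it. Under assumed resolution of 20 and 40 % of the diagnosed and none of the undiagnosed, the PAL-alone ratio falls from 2.00 to 1.55 and power from 79 to about 30 % at a between-cluster CV of 25 %. PAL alone is the exposed comparison because the plan itself expects only about 80 % power for it. PAL + IHP keeps at least 89 % power in every scenario tabulated. Every resolution share is an assumption.

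The cough versus cough/wheeze mismatch is a real but smaller inconsistency. If cough alone gave 80 or 70 people per cluster (assumed values), PAL-alone power would be 72 or 68 %. None of this requires replacing the primary outcome. It does call for an analysis that does not condition on cough.

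**What to change.** - Keep the stated primary outcome.
- Pre-specify a supportive analysis of diagnoses of TB or airway disease recorded in the health passport since intervention start, with all surveyed people aged 15 and over as denominator (about 9,072 per arm, who are interviewed anyway).
- Report the prevalence of chronic cough at follow-up by arm, so that a shift in the denominator is visible.
- Use one symptom definition, either cough or cough and/or wheeze, in both the outcome and the sample-size section.
- Optionally, add a sensitivity analysis whose denominator is cough at any time since implementation, with the recall limitation stated.

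The cost is inspecting passports and noting the diagnosis date for more respondents, plus one recall question if the optional analysis is added. The all-adult proportions are small (around 0.5 to 2 % under the plan's own assumptions), so precision will be lower; this is why the analysis is proposed as supportive.
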